### Online Programs

#### Program Content, Tone, and Design

The content of the *Baby Steps* programs, *Babycare* and *Well-being,* was developed by a team comprised of clinical psychologists, midwives, and a neonatologist. *Baby Steps* is a modular, self-paced program designed to provide infant care and well-being information, and tools relevant for mothers and fathers during late pregnancy until their infant is approximately six months of age. Each module contains 4-8 categories that help to guide program users through the information contained within the module, or information presented through external websites and programs. Suggestions are offered for employing the information and tips individually, as parent and infant, as a couple, or as a family. A *Get Help* tab includes links to other parenting websites and programs, and links to face-to-face, telephone, or online health service providers.

Program information is written in an encouraging and non-judgmental tone, designed to create an empathic environment in which new parents can access information and tools. Inclusive language is used to aid engagement of both mothers and fathers in the program and gender role assumptions have deliberately been avoided when presenting the content. For example, information about returning to work after a brief leave is provided for both mothers and fathers, as are tips and suggestions for helping to feed an infant. Photos and images of both men and women interacting with their infants are used throughout the program.

#### Babycare Program – Control Condition

The *Babycare* program is comprised of four modules: (1) *Getting Prepared* – practical tools to help expectant parents prepare for the arrival of an infant, (2) *Feeding* – information about breastfeeding, formula feeding, and combined feeding, (3) *Improving Baby’s Sleeping Habits* – information for understanding the patterns of infants’ sleep and sleep cues, plus practical tools for creating a sleep routine, and (4) *Soothing* – information and practical techniques to calm a crying infant.

##### Short Message Service Reminders

Automated short message service (SMS) texts will be sent to *Babycare* participants two, four, seven, and ten weeks after program allocation to remind them to log into the program.

#### Well-Being Program – Experimental Condition

*Babycare* is an information-only program, while *Well-being* is an interactive program including the four *Babycare* program modules along with five additional modules promoting parental well-being, and utilizes interactive tools for the enhancement of well-being. The five additional modules are: (1) *Self-Care* – information and tips to assist new parents to look after their physical and mental health, (2) *Relationships* – tools for working through changes in the romantic relationship after an infant is born, (3) *Interacting with Baby* – information to assist new parents to understand, bond with, and play with their infant, (4) *Changing Roles* – tips to assist new parents to adjust to the new roles that parenthood brings, and (5) *Especially for Fathers* – well-being and infant care information targeted specifically to fathers.

After qualitative interviews with mothers and fathers who trialed the *Baby Steps* programs, the *Especially for Fathers* module was developed to provide additional father-targeted information. However, this module is also available to mothers who may wish to understand the role of fathers, and provides useful tips for his well-being.

##### My Plans

Within each module, *Well-being* participants can choose tips to send to the *My Plans* tool, which functions as a goal-setting, problem-solving, and behavioral activation tool. Participants are encouraged to develop plans to incorporate the chosen tips into their lives, including setting a specific date and time when the plan will be attempted, or a regular frequency at which they will complete the plan. Example suggestions for plans that may be attractive to mothers, fathers, or both parents are distributed throughout the modules. A participant using the *Self-Care* module could select the *Talk to someone about what’s stressing you* tip, and choose to develop a plan to *Book an appointment with my General Practitioner* and to complete the plan on *November 10*^th^*.* Participants are able to review and update their plans throughout their use of the program, and can mark plans as completed.

##### Additional Tools

The *Well-being* program also includes a *Scrapbook* tool, in which participants can upload and view photos that remind them of pleasure and success. The participant’s personalized *Dashboard* displays *Scrapbook* photos, upcoming plan due dates, rotating module tips, and light-hearted, infant-specific trivia questions.

##### Short Message Service Reminders

Participants allocated to the *Well-being* program will also receive automated SMS texts two, four, seven, and ten weeks after allocation, reminding them to log into the program, select useful tips, develop plans to enhance well-being, and regularly review the progress of their plans.

### Intervention Integrity

Reporting of this study is guided by the Consolidated Standards of Reporting Trials statement [52] and international best practice. The randomization schedule is concealed within a secure database accessible only to the Goji development manager. Researchers collecting post-baseline assessments will be blinded to condition. Calls made to welcome participants to the study, or to conduct a risk assessment, will be made by a researcher blind to treatment allocation. Data analyses will be conducted based on the principle of intention-to-treat [53].

### Study Measures

Measures will be restricted to minimize the burden on participants. Demographics collected will include details of income and occupational engagement. Economic information including healthcare data, work time/productivity data, and intervention establishment/delivery data will also be collected. Past and recent psychiatric history will also be assessed. Information concerning the outcome of the pregnancy will be collected 13 weeks post-baseline. The EPDS [54] will be used to assess perinatal distress and the four-item Social Support Survey [55] will measure satisfaction with social support. The Assessment of Quality of Life-8 Dimensions (AQol-8D) [56] will be used to assess quality of life, and relationship satisfaction will be measured by the Couples Satisfaction Index [57].

Three measures were designed specifically for this study. These measures were created to be brief, as to minimize time burden on participants, and designed to directly measure certain program components. Self-efficacy over the initial 13 weeks of child-rearing, and providing support to a partner (ie, *feeding your baby*, *putting your baby to sleep*, *settling your baby*, *providing support to your partner*), will be assessed on an 11-point scale. The scale increases in 10-point increments, and ranges from 0 (not at all confident) to 100 (extremely confident). Current satisfaction with participants’ parenting role and skills, and with relationships and social support (ie, *relationship with their partner*, *support received from and given to their partner*, *practical and emotional support received from others*), will be rated on a similar 11-point scale from 0 (not at all satisfied) to 100 (extremely satisfied). The same rating scale will be used for program satisfaction at 13 weeks post-baseline (ie, *overall*, *relevance*, *usefulness*, *how easy it was to find what they wanted*). Timing of the assessments is presented in Table 2.

**Table 2 table2:** Study measures and timing.

Measure	Domain	Baseline	13 week follow-up	26 week follow-up
Demographics	Demographics			
Work history and performance	Recent employment history and performance			
Birth items	Baby and birth details			
AQol-8D	Quality of life/well-being			
Edinburgh Postnatal Depression Scale	Perinatal distress			
Self-efficacy items	Parental self-efficacy			
Satisfaction items	Satisfaction			
Social Support Survey	Social support			
Couples Satisfaction Index	Relationship satisfaction			
Psychiatric history	Psychiatric history			
Recent medical history	Medical history, healthcare data			
Program satisfaction items	Program satisfaction			
Program use	Program engagement			

Both *Baby Steps* programs automatically collect program use data that are summarized into engagement variables (number of logins, module pages viewed, number of plans made, number of photos uploaded to the Scrapbook, and total time spent on the module pages).

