#### Inclusion Criteria

Participants will be included in the trial if they are a co-parenting male-female couple aged 18 years or older, this is the first child for both parents, gestation is between 26 and 38 weeks at registration (couples registering before 26 weeks of gestation will be reminded by email to retake the screening survey when they reach the 26-week time point), and the pregnancy involves a single child. Participants must also be literate in English, have Internet and mobile phone access, and complete the baseline assessment. Both parents must be eligible for the couple to participate. Exclusion criteria are presented in Figure 1.

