#### Screening and Baseline

Couples will register for the study by creating a website account for each user with email addresses and passwords. Registrants will then be individually emailed with a link to the screening survey, in which the trial information statement is provided. Participants will confirm that they have read and understood the statement, and that they consent to participate in the research before continuing. Participants will then complete the screening survey to confirm that they meet the study inclusion criteria. Eligible participants will be directed to the online baseline assessment survey, and both parents must complete the survey before the couple is randomly assigned to an intervention condition. Registrants who are not eligible for the study will still be able to access the *Babycare* program.

Reminder emails will be sent to registered participants on an automated schedule if they or their partner have not completed the screening survey three days post-registration, or the baseline survey three days post-screening. If the survey is still not complete 10 days post-registration, participants will be contacted by a research officer to assist with completion of the survey (if the couple gives ongoing consent to participate). If both individuals have not completed the baseline assessment four weeks after eligibility is confirmed, couples will be withdrawn from the study and offered access to the *Babycare* program. After completion of the baseline assessment and randomization, couples will be telephoned by a researcher (blind to treatment allocation) to welcome them to the study, collect postal address details, and provide the research team’s contact information.

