#### Follow-Up Assessments

Follow-up assessments will be at 13 and 26 weeks post-baseline. For the purposes of these assessments, couples will be treated as individual participants and emailed an individualized online survey link. To maximize retention, participants will be reminded to complete the survey via scheduled emails. If the participant has not responded within two weeks of the due date, a researcher (blind to treatment allocation) will phone the participant, establish ongoing consent from the participant, and attempt to obtain the assessment over the phone. Participants will be offered an AUD $20 gift voucher (AUD $40 per couple) for completing each follow-up assessment.

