#### Randomization

Allocations will be generated by the Goji program, a web-based research trials management system developed at Queensland University of Technology, Australia, by the same web developers who programmed the *Baby Steps* programs. When the researcher notifies Goji that a participating couple has completed their baseline assessment, Goji will allocate the participants to a research group, randomizing couples as a unit. Randomizations will be in permuted blocks, and stratified by scores on the EPDS: neither parent distressed (father <5; mother <7) versus either parent distressed (father >5; mother >7). These cut-off scores represent optimum screening levels for depressive or anxiety disorders in fathers and mothers [7]. After randomization, a couple’s access to the allocated program will be granted by a researcher not blind to treatment allocation, and participants will be notified by email that they are able to log into the online program through their registered account.

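### Follow-up is timed from baseline while entry spans 26 to 38 weeks' gestation, so the 13-week occasion mixes a few couples still pregnant with parents of infants up to about 11 weeks old, and the stated adjustment rule would not remove that variation

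*Protocol article*

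**What the plan says.** Under Inclusion Criteria, couples qualify when "gestation is between 26 and 38 weeks at registration". Those who register earlier "will be reminded by email to retake the screening survey when they reach the 26-week time point", so some entries may collect at the lower limit. Screening and Baseline allows a delay before baseline: "If both individuals have not completed the baseline assessment four weeks after eligibility is confirmed, couples will be withdrawn from the study". The follow-up clock then starts at baseline: "Follow-up assessments will be at 13 and 26 weeks post-baseline".

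Study Measures places birth data on that clock: "Information concerning the outcome of the pregnancy will be collected 13 weeks post-baseline". One outcome set is worded for the time after birth: "Self-efficacy over the initial 13 weeks of child-rearing, and providing support to a partner". On allocation, "Randomizations will be in permuted blocks, and stratified by scores on the EPDS"; gestation is not a factor. Descriptive Analyses says that baseline variables will be compared between groups and that differences found will be adjusted for. Primary and Secondary Analyses names mixed models and mentions neither gestation nor infant age.

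**The concern.** The entry window is 12 weeks wide and the first follow-up comes 13 weeks after baseline. A single nominal occasion can therefore hold late-pregnancy scores, scores from the first days after birth, and scores from nearly three months postpartum. The EPDS is a primary outcome and the powered test is the Time x Condition interaction, so what the middle level of Time represents matters for reading the result. Spread in infant age is also a source of outcome variance that has nothing to do with the program. The stated adjustment rule acts only on imbalance between arms. Randomization makes balance on gestation the expected case, so the rule will usually leave this variance in place.

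**Working it through.** **The plan's own figure.** The only computed figure nearby is the power of .80 (Sample Size). With N = 240, three occasions, f = 0.082, and an assumed within-person correlation of 0.5 with sphericity (neither is stated), lambda = 240 x 3 x 0.082^2 / (1 - 0.5) = 9.68. On 2 and 476 df this gives power 0.799, so the figure reproduces. The present point does not depend on it.

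**Timeline.** Inputs from the article: gestation at registration 26 to 38 weeks; lag from eligibility to baseline 0 to 4 weeks; follow-up at +13 and +26 weeks. Gestation at birth is not given; 40 weeks is assumed, with a range of 37 to 42. The lag is counted from registration, which takes screening as immediate.

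Infant age = gestation at entry + lag + 13 (or 26) - gestation at birth.

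| Entry | Lag | 13-week occasion | 26-week occasion |
|---|---|---|---|
| 26 | 0 | 26 + 13 - 40 = -1 | 26 + 26 - 40 = 12 |
| 38 | 0 | 38 + 13 - 40 = 11 | 38 + 26 - 40 = 24 |
| 26 | 4 | 26 + 4 + 13 - 40 = 3 | 26 + 4 + 26 - 40 = 16 |
| 38 | 4 | 38 + 4 + 13 - 40 = 15 | 38 + 4 + 26 - 40 = 28 |

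The 15-week figure needs a baseline at 42 weeks, two weeks after a 40-week birth. If every baseline precedes the birth, infant age at an on-time first follow-up cannot exceed 13 weeks. A couple is still pregnant at that follow-up if baseline falls before 27 weeks (birth at 40) or before 29 weeks (birth at 42).

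**Share still pregnant at the 13-week occasion.** Assumptions: gestation at birth normal, entry spread as shown, couples delivered before baseline left out, follow-up answered on the due date. Each cell is a range over birth at mean 39.5 (SD 1.5) and mean 40 (SD 1.3) weeks.

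| Entry pattern | Lag 0 | Lag 1 week | Lag 2 weeks | Lag 4 weeks |
|---|---|---|---|---|
| Even, 26-38 weeks | 7-10% | 3-4% | 1-1.5% | <0.1% |
| 25% exactly at 26 weeks, rest even | 21-27% | 12-16% | 5-7% | 0.3% |
| Even, 28-36 weeks only | about 2% | 0.4% | <0.1% | 0% |

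Under even entry with no lag, 7.4-9.7% is about 18-23 of 240 couples. Answering two weeks late acts like two more weeks of lag: the 7-10% becomes about 1%.

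**Spread of infant age.** Even entry over 12 weeks has SD 12/sqrt(12) = 3.46 weeks. Adding birth variation with SD 1.5 gives sqrt(12 + 2.25) = 3.8. Simulation that leaves out couples delivered before baseline gives 3.4-3.7 weeks for even entry and lags of 0-2 weeks, 3.9-4.2 with the cluster at 26 weeks, and about 2.6-2.8 if entry is confined to 28-36 weeks.

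**The case against.** The strongest defence is that timing from baseline is deliberate. The hypotheses are stated at 13 and 26 weeks post-baseline, reminders run from allocation, and the programs cover late pregnancy to about six months of infant age. This clock holds exposure time roughly constant, and perinatal distress spans birth. That stands: the clock is a defensible choice and the protocol nowhere calls the 13-week occasion postnatal for everyone. What it does not answer is the unmodelled spread that the choice creates.

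A reader might infer several stronger things that the document does not support:

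- **Birth outcome is lost for the earliest entrants.** The text names 13 weeks but does not exclude a later request. Table 2 has a row for birth items and a 26-week column, and its timing marks could not be read in the copy reviewed.
- **Some baselines are completed after birth.** The dates allow it, but the exclusion criteria are in Figure 1, which was not available, and may rule it out. High shares still pregnant and high shares with late baselines also need opposite lags, so they cannot both occur.
- **The arms are biased.** Randomization balances gestation in expectation.
- **Self-efficacy cannot be rated before birth.** The items rate confidence, which expectant parents can give. It is then expectation and not experience.
- **A missing covariate is itself a fault.** A covariate list may sit in an analysis plan that is not shown. The criticism here is of the adjustment rule that the article does state.

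The share still pregnant is also small under most assumptions, and late responses shrink it further ("If the participant has not responded within two weeks of the due date, a researcher (blind to treatment allocation) will phone the participant").

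**Conclusion.** The point holds as one of precision and interpretation. On the protocol's own dates the 13-week occasion covers infant ages from about -1 to 11 weeks (15 with the full lag) if birth is at 40 weeks. About 0-10% of couples would still be pregnant under even entry. The share would be higher only if the call-back at 26 weeks produced a real cluster with prompt baselines, and lower if entry centred later. Infant age would have an SD of roughly 3 to 4 weeks. How much this inflates outcome variance cannot be computed, because the article does not say how steeply the EPDS or self-efficacy changes with infant age. The effect is added noise and a less clear 13-week estimate, with no bias between arms. Adjustment triggered by detected imbalance does not address it.

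**What to change.** 1. Replace reliance on detected imbalance, for this variable, with a pre-specified term: gestation at baseline and its interaction with time, in every outcome model whether or not the arms differ. It is fixed before randomization, and screening must already ask for gestation to apply the entry rule; elapsed time to baseline is added. The cost is a few degrees of freedom.
2. Keep the primary analysis intention-to-treat in all randomized participants. Add a supportive sensitivity analysis limited to 13-week assessments made after birth, using the birth details. Delivery status is known only after randomization, so this restriction should not define the primary analysis of any outcome, self-efficacy included.
3. Check Table 2. If the 26-week survey does not already carry the birth items, ask them there of anyone undelivered at 13 weeks. The downside is a few extra items for a handful of participants.

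Recruitment ended in October 2015 and follow-up was to run to May 2016. Items 1 and 2 change only the analysis. Item 3 helps only couples who had not yet reached their 26-week survey.

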### Data Analyses

Version 22 of the IBM SPSS Statistics program will be used to perform all data analyses.

#### Descriptive Analyses

Baseline data from the two program groups will be compared to check for comparability of the groups. Chi-square tests will be used for categorical variables, ANOVA tests for normally distributed continuous variables, and Kruskal-Wallis tests for non-parametric data. Any differences detected will be controlled for during the subsequent analyses.

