#### Sample Size

A total of 240 couples (120 couples per group) will be recruited. A sample size of 240 will give a power of .80 for detecting a significant *Time* x *Condition interaction* (*P*<.05) over three occasions of measurement, with a small effect size of f=0.082 [50,51].

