#### Primary and Secondary Analyses

All data analyses will be based on the intention-to-treat principle [53]. Continuous outcomes (eg, measures of perinatal distress, quality of life, couple relationship satisfaction) will be analyzed using general linear mixed models, and multilevel modelling will be used for nested data, to deal with any missing data.

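### Covariates are to be chosen by baseline significance tests, a rule that follows chance imbalance and would almost never bring in the EPDS stratum

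*Protocol article*

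**What the plan says.** In the protocol article, Descriptive Analyses opens with the purpose of the baseline comparison: "Baseline data from the two program groups will be compared to check for comparability of the groups". It then names the tools: "Chi-square tests will be used for categorical variables, ANOVA tests for normally distributed continuous variables, and Kruskal-Wallis tests for non-parametric data". It ends with a commitment: "Any differences detected will be controlled for during the subsequent analyses". No significance threshold, list of variables or unit of analysis is given for these tests.

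The Randomization section says: "Randomizations will be in permuted blocks, and stratified by scores on the EPDS". The two strata are couples with neither parent distressed and couples with either parent distressed. Couples are allocated as a unit, after both partners have completed the baseline survey.

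Primary and Secondary Analyses says that continuous outcomes "will be analyzed using general linear mixed models, and multilevel modelling will be used for nested data, to deal with any missing data". It names no covariates and no stratification term, so the sentence in Descriptive Analyses is the only covariate rule in the article.

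**The concern.** Baseline data are complete before allocation, so the arms can differ at baseline only by chance. A small p-value then shows that chance produced an imbalance. It does not show that the variable predicts outcome, which is the reason to adjust for it. Three consequences follow.

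- The covariate set, and so the model for the primary outcomes, is known only after the arms have been compared. Two analysts following the sentence faithfully could fit different models.
- Strong predictors that happen to be balanced stay out, and weak ones that happen to be imbalanced go in.
- The EPDS stratum is kept balanced by the blocking, so a test will hardly ever flag it. It is built from the instrument that measures the primary distress outcome, so it is very likely prognostic. A model without it does not use the precision that the stratified design provides.

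Precision is at stake in a trial planned at 0.80 power for a small effect, and so is having the model fixed before the data are seen.

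**Working it through.** **1. The plan's own figure.** Sample Size gives 240 couples, three occasions, f = 0.082, P<.05 and power 0.80 for the Time x Condition interaction. For a within-between interaction, lambda = f² × N × m / (1 − rho). The correlation rho is not stated; 0.5 is assumed. Then lambda = 0.006724 × 240 × 3 / 0.5 = 9.68, with 2 and (240 − 2) × 2 = 476 degrees of freedom, and power is 0.799. The figure reproduces, and nothing below changes it.

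**2. How often the rule fires.** Table 2 has 13 rows. Birth items, program satisfaction and program use are post-baseline by nature, which leaves about 10 domains, or 20 tests if mothers and fathers are tested separately. A 5% threshold and independent tests are assumed. The probability of at least one chance difference is 1 − 0.95^k:

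- k = 10: 1 − 0.95^10 = 0.401, with 10 × 0.05 = 0.5 false selections expected
- k = 20: 1 − 0.95^20 = 0.642, with 20 × 0.05 = 1.0 expected
- for range: 0.34 at k = 8 and 0.79 at k = 30

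**3. Whether the rule would select the stratum.** Simulation, 4,000 runs per scenario. Assumed settings: 240 units, stratified blocks of 4, 40% of couples in the distressed stratum, 10 independent baseline variables of which two are prognostic (coefficient 0.3), and a correlation of 0.5 or 0.7 between baseline and follow-up. The rule selected at least one variable in 39% to 41% of runs. It selected the stratum in 0 of 4,000 runs in every scenario.

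**4. What that does to the comparison at follow-up.** Power is at a difference of 0.36 SD.

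| Model | Type I, corr. 0.5 | Power, corr. 0.5 | Type I, corr. 0.7 | Power, corr. 0.7 |
|---|---|---|---|---|
| No covariates | 0.043 | 0.809 | 0.034 | 0.822 |
| Test-based rule | 0.039 | 0.810 | 0.032 | 0.822 |
| Rule plus stratum | 0.046 | 0.835 | 0.049 | 0.871 |
| Stratum only, prespecified | 0.050 | 0.833 | 0.054 | 0.867 |
| Stratum and baseline score, prespecified | 0.052 | 0.900 | 0.053 | 0.976 |

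The Monte Carlo standard error at 0.05 is √(0.05 × 0.95 / 4000) = 0.0034. The shortfall under the rule is therefore real, and the rows with the stratum are compatible with 0.05.

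The mechanism shows in the model without covariates. With unit outcome variance its standard error is about √(1/120 + 1/120) = 0.129, while the estimate actually varied with SD 0.124 (correlation 0.5) or 0.119 (correlation 0.7). The reported standard error is too large by about 4% or 8%.

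**5. The contrast closest to the planned interaction.** On change from baseline in the EPDS-like score, type I error was 0.042 and 0.047 without the stratum (correlations 0.5 and 0.7) and 0.052 and 0.053 with it. Power went from 0.805 to 0.830 and from 0.956 to 0.960. The softening depends on the correlation. The share of variance tied to the baseline score is rho² for the follow-up score (0.25 and 0.49) and (1 − rho)² / (2 − 2 rho) for change (0.25 and 0.15). It falls at 0.7 but not at 0.5.

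**The case against.** The strongest reply is that this is a condensed article, and that naming the stratum as a model term is commonly left to the full protocol or analysis plan. The article says that detected differences will be controlled for; it does not say that only those will be. That stands: a reader might infer that the stratum is excluded, and no section says so. It does not rescue the sentence itself, which is a positive commitment. An analysis plan that followed it would inherit the fault, and one that replaced test-based selection with a fixed covariate list would contradict it.

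A reader might also infer inflated false positives or bias, since the model is chosen after looking at the data. The simulation shows neither: the error is on the conservative side.

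A third tempting inference is that the baseline tests treat the two partners of a couple as independent. The article does not give the unit of these tests. They could be run by parent or by couple, and multilevel modelling is planned for nested outcome data, so this is not part of the point.

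The 40% and 64% figures are open to challenge as well. The timing cells of Table 2 are blank in the available text, domains are not tests, and scores on distress, quality of life and relationship satisfaction are unlikely to be independent. They are illustrations. A 40% chance of one added covariate is also not a 40% chance of a wrong conclusion.

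Finally, the power of 0.90 to 0.98 in the last table row comes mainly from adding the baseline score, so it does not measure the harm done by the rule.

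**Conclusion.** The point holds as a fault in a stated rule. Selecting covariates by baseline tests makes the model depend on the data, ignores prognosis, and would almost never bring in the stratum used for randomisation. Under the assumed settings the cost at follow-up is a type I error of 0.032 to 0.039 instead of 0.05, and 2.5 to 5 percentage points of power (0.810 against 0.835, and 0.822 against 0.871). For EPDS in the three-occasion model the cost can be smaller, clearly so only when the correlation between occasions is well above 0.5. Block size, stratum share, number of variables and correlations are all assumptions. The stated sample size is unaffected. To say that omitting the stratum invalidates the analysis would go too far: what is lost is precision and a model fixed in advance. The change should be made, but the trial does not stand or fall by it.

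**What to change.** Delete the sentence on controlling for detected differences, drop the baseline tests, and report baseline data descriptively by arm. Prespecify the covariates for every outcome: the randomisation stratum as allocated, and parent role.

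Use the baseline outcome once. Either keep it as one of the three repeated occasions, as Sample Size implies, or model the two follow-ups with baseline as a covariate; it should not be both response and covariate. In the three-occasion model, enter the stratum with its interaction with time, because with complete data a main effect alone leaves the Time x Condition contrast unchanged. Gestation is optional.

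The cost is a change of wording in the analysis section, plus a decision on which of the two model forms is meant. No new data or participants are needed. The downside is that the baseline p-values are lost, and a chance imbalance in some other variable is handled only through the prespecified covariates or a sensitivity analysis labelled as such.
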